## Abstract

**Background:**

Cognitive impairment is seen in up to three quarters of heart failure (HF) patients and has a significant negative impact on patients’ health outcomes. Prospective memory, which is defined as memory to carry out future intentions, is important for functional independence in older adults and involves application of multiple cognitive processes that are often impaired in HF patients. The objective of this study is to examine the effects of prospective memory training on patients’ engagement in HF self-care and health outcomes, carer strain and quality of life.

**Methods/design:**

The proposed study is a randomised, controlled trial in which 200 patients diagnosed with HF, and their carers will be recruited from 3 major hospitals across Melbourne. Eligible patients with HF will be randomised to receive either: 1) The Virtual Week Training Program - a computerised prospective memory (PM) training program (intervention) or 2) non-adaptive computer-based word puzzles (active control). HF patients’ baseline cognitive function will be compared to a healthy control group (n = 60) living independently in the community. Patients will undergo a comprehensive assessment of PM, neuropsychological functioning, self-care, physical, and emotional functioning. Assessments will take place at baseline, 4 weeks and 12 months following intervention. Carers will complete measures assessing quality of life, strain, perceived control in the management of the patients’ HF symptoms, and ratings of the patients’ level of engagement in HF self-care behaviours.

**Discussion:**

If the Virtual Week Training Program is effective in improving: 1) prospective memory; 2) self-care behaviours, and 3) wellbeing in HF patients, this study will enhance our understanding of impaired cognitive processes in HF and potentially is a mechanism to reduce healthcare costs.

**Trial registration:**

Australian New Zealand Clinical Trials Registry #366376; 27 May 2014. https://www.anzctr.org.au/Trial/Registration/TrialReview.aspx?id=366376&isClinicalTrial=False.

## Background

Heart failure (HF) is a chronic syndrome with multiple symptoms that impose a significant burden on the individual and healthcare system [1]. The prevalence of HF is estimated at 23 million individuals worldwide and despite advances in management there remains substantial risk for high morbidity and mortality [2]. Cognitive impairment, which has been found to occur in up to 75% of HF patients [3], is a comorbidity that is gaining increased recognition as adding to HF morbidity and mortality [4,5].

There is compelling evidence demonstrating that HF patients are more vulnerable to changes in brain processes (memory, thinking, and thoughtful decisions) than similar matched individuals without HF [6]. Furthermore, almost three quarters of HF patients have evidence of cognitive impairments, especially memory, when brief cognitive screening questionnaires have been applied [3]. The impact of cognitive impairment in this vulnerable group of patients is significant as it also contributes to worse health outcomes, poor engagement in self-care and increased mortality [5,7,8].

Optimal self-care is considered an important non-pharmacological aspect of HF management that stabilises symptoms and improves health outcomes [7]. Key self-care behaviours include adhering to prescribed HF therapies including medications, dietary sodium and fluid restrictions, and exercise [9]. As well as adhering to these HF therapies, patients are taught to recognise and manage changes in symptoms, and seek health advice when such changes occur [9].

The significant research attention addressing methods to optimise HF self-care has also drawn attention to a host of barriers that have the potential to impede achievement of this outcome [10,11]. In recognising these barriers, it may not be feasible for all patients to develop adequate self-care skills [12].

Cognitive impairment is a key barrier to HF patients’ self-care as it has a negative impact on patient’s ability to engage in effective self-care behaviours, including initiating an appropriate and timely response to changes in HF symptoms [5,13]. The patient’s cognitive ability to respond to vital cues and initiate appropriate actions is not only critical in predicting engagement in self-care, it is frequently overlooked, with poor engagement in HF self-care often considered to reflect poor motivation and/or compliance [5].

Particularly relevant to cognitive ability is prospective memory (PM), currently a topic of intense interest in ageing and neuropsychology [14,15], although as yet given limited attention from the standpoint of HF. Described as remembering to carry out future intentions [16], PM includes many of the cognitive functions necessary in forming and initiating HF self-care decisions. One example specific to HF patients is that they: i) form the intention to weigh themselves daily, ii) hold on to this intention and conduct this behaviour each morning, and iii) initiate the appropriate action (reduce daily intake of sodium and fluids) in the event of a > 2-kg weight change. Thus, PM is not so much one specific cognitive process, but a set of cognitive processes involved in forming, retaining, initiating and executing an intention [17]. Successfully performing PM tasks requires intact functioning of multiple cognitive domains that are often impaired in HF patients [8]. These domains primarily include: attention; working memory; retrospective memory; and executive functioning [18].

The three leading theories as to why HF patients are vulnerable to cognitive changes are: i) chronic or intermittent hypoperfusion leading to cerebral ischaemia [19]; ii) microemboli causing cerebral infarction [20]; and iii) hypoxia arising from sleep apnoea [21,22]. However, in a recent review on cognitive impairment and cardiovascular disease [23] it was acknowledged that normal brain function requires seven interlinking physiological aspects to be intact: heart; lungs; elastic vessels; baroreflex; cerebrovascular arteries; small cerebral vessels; and cerebrospinal venous system. Conditions affecting these cardiovascular organs are often mutually interrelated, such that when one is anatomically or functionally altered it can lead to impaired cerebrovascular perfusion and increased risk of neurocognitive impairment. In functional neuroimaging studies of HF patients the most frequently damaged areas are the cortical white matter, particularly in the frontal lobes, and subcortical grey matter nuclei, particularly the thalamus, basal ganglia and brainstem [24-27]. The neural substrates in these regions of the brain are responsible for cognitive control operations and executive control. However, the temporal lobes of the brain may also be disrupted [26]. The temporal lobes play a key role in retrospective memory, which is critical for PM. Based on current evidence, it is likely that HF patients will have significant deficits in PM that are likely to impact on their everyday functioning.

Studies have demonstrated that PM is critical for maintaining functional independence in older adults [28] and PM tasks are sensitive to abnormal ageing [29]. The PM literature distinguishes between event-based tasks (for example, taking extra diuretic if weight changes by > 2 kg) and time-based tasks (for example, weighing at set times). One of the most valid assessment tools for measuring PM is Virtual Week; a computer program designed to simulate real world activities to test PM [30]. In preliminary analysis using Virtual Week to assess PM, we found that, compared with aged-matched healthy controls, HF patients had significant deficits across all types of PM tasks, even on those that minimised the demands for remembering the content of the task [31]. Because of the potential impact on health outcomes, PM represents a promising domain for cognitive training [32]. While much of the PM research has focused on ageing [28,29], and even though it is established that cognitive ability is often limited in HF patients, research to date is yet to investigate PM among this clinical cohort. This study is the first of its kind to do so and, in addition, to identify the potential of cognitive training to promote HF self-care. Further, we aim to examine whether carer burden (strain, perceived control and quality of life) changes in line with changes in PM of the HF patient.

In the area of cognitive training two main approaches have typically been investigated: 1) strategy-based training, which aims to compensate for limitations in underlying cognitive processes, and 2) process-based training, which aims to restore underlying cognitive processes that are impaired. These training studies have improved performance on the specific tasks used in training (near transfer) but have resulted in limited evidence for training gains to transfer to activities that are not closely related to the training task (far transfer) [33]. Furthermore, recent reviews have argued that cognitive training programs have typically implemented tasks that bear little resemblance to everyday life. For example, a working memory task such as learning a list of words may have little resemblance to adhering to HF self-care behaviours such as daily weighing and taking prescribed medications. Researchers have advocated the need for more ecologically valid training programs that target abilities such as PM [32], which is critical for maintaining functional independence [28]. Despite the importance of PM in daily life, there have been only a few small-scale training studies that have targeted PM [33]. The Virtual Week Training Program is a computerised program designed to simulate real world activities to test and improve PM [30]. The Virtual Week Training Program is a computerised extension of the standard Virtual Week program for assessing PM [30] that has a board game format with each circuit of the board simulating a day. Embedded within the game are hypothetical PM tasks that closely represent PM tasks in daily life, such as taking medication with meals and attending appointments at specific times (for example, 5 pm).

Preliminary findings using a 4-week version of the Virtual Week Training Program with healthy older adults had promising effects for both laboratory-based PM skills practiced (near transfer) and pragmatic PM tasks performed in everyday life (far transfer) [33]. Fifty healthy older adults participated in either the Virtual Week Training Program, an active control (involving music training) or a passive control. After the training, participants in the Virtual Week training group showed greater improvement in a real-life PM task, the call-back task, compared to both no-contact and active control groups, suggesting there was some transfer to performing PM tasks in the real world. Furthermore, participants in the Virtual Week training group showed a greater pre- to post-test improvement in Timed Instrumental Activities of Daily Living (TIADL) after PM training compared to both control groups, indicating far transfer [33]. We aim to extend these preliminary findings by examining the efficacy of a 6-week PM training program using the Virtual Week Training Program among HF patients. The impact of Virtual Week training will also be examined with regard to carer strain and quality of life. Furthermore, our comprehensive assessments of cognitive functioning will enable us to examine near to far training benefits in everyday functioning.

### Rationale for study

Although cognitive impairment among HF patients has received considerable attention, this will be the first study to specifically examine PM among this clinical group. This study will add evidence for the impact of cognitive impairment on HF patients and their carers by examining how PM relates to patient engagement in HF self-care and health outcomes. This study will also provide evidence for the feasibility of a novel computer-based memory training program (the Virtual Week Training Program) and will test whether this improves functional outcomes among HF patients.

### Study aims and objectives

We will conduct a randomised controlled trial to:compare and confirm cognitive deficits, including PM deficits, of HF patients relative to healthy matched control group;examine if PM is a significant predictor of HF self-care;test the feasibility of implementing the innovative restorative memory training;examine if PM training, using the Virtual Week Training Program, improves self-care and functional outcomes among HF patients (near to far transfer effects) and reduces hospital readmissions;examine if PM training of HF patients changes their careers’ burden (strain, perceived control and contribution to patient HF self-care) and enhances their quality of life.

### Hypotheses

We hypothesise that the cognitive training will result in improved functioning, better health outcomes and reduced healthcare costs in this patient group. In addition, we predict that the improved functioning of the HF patients will reduce levels of carer burden (strain, perceived control, contribution to patient HF self-care) and improve their quality of life.

## Methods/design

### Study design

This will be a randomised controlled trial where 200 patients with HF will be randomised to receive either: 1) the Virtual Week Training Program, a computerised adaptively difficult PM training program, or 2) non-adaptive computer-based word puzzles. Sixty healthy control participants, with no HF diagnosis, will also be assessed to compare differences in baseline measures of cognitive and psychosocial functioning. There are 4 phases to the study: 1) baseline testing; 2) 6 weeks of cognitive training; 3) Assessment One, 2 to 4 weeks post cognitive training; and 4) Assessment Two, 12 months post cognitive training. There will be two separate interviews during each of the assessments (baseline testing, Assessment One and Assessment Two). These will be: a) nursing assessment including physical functioning, and self-care; and b) PM and neurocognitive assessment, and TIADL.

### Setting

Participants will be recruited from three major metropolitan hospitals in Melbourne, Australia.

### Participant inclusion criteria

A total of 200 HF patients aged 18 years or older will be recruited. Inclusion criteria will be: diagnosis of HF with reduced ejection fraction (ejection fraction < 45% in the previous 2 years) as confirmed by a cardiologist and consistent with Australian guidelines [34]; attendance at a specialist HF clinic or rehabilitation program, and/or a disease management program with nursing follow-up and able to participate in the study (that is adequate vision, hearing and English comprehension). Carers will be identified by HF patients as someone who is familiar with and contributes to the management of their heart condition (for example, a partner, family member, friend or next of kin). Patients who cannot identify a carer will still be eligible to participate in the study. All HF patients enrolled in the study will continue to receive usual care which can be from any combination of nurse-led chronic disease management programs, specialised HF outpatient clinics, or outpatient rehabilitation programs. A key aspect of usual care is patient education and support from a multidisciplinary team that is directed at promoting self-care maintenance and monitoring behaviours. Healthy control participants will be living independently in the community without a medical diagnosis of HF and have adequate performance on the Addenbrooke’s Cognitive Examination Revised (ACE-R) [35].

### Participant exclusion criteria

Patients will be excluded if they: do not have access to a PC computer; do not have basic computer skills or do not have the physical ability to use a computer keyboard; reside in a long-term high-care facility (nursing home); have a documented history of moderate-to-severe cognitive impairment or dementia, a cerebrovascular accident, acute myocardial infarction or have undergone cardiac surgery in the previous 3 months; or have a terminal diagnosis. Carers will be excluded if they have a documented history of moderate-to-severe cognitive impairment or dementia or have a terminal diagnosis. Healthy control participants will be excluded if they: reside in a long-term high-care facility (nursing home); have moderate-to-severe cognitive impairment or dementia; or have experienced a cardiac event within the past 6 months (cerebrovascular accident, acute myocardial infarction or cardiac surgery).

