
In a second interview, HF patients will undergo comprehensive PM and neurocognitive assessment, and TIADL, which will take 90 to 120 minutes to complete. The second interview will include the following:I.*Global cognitive screen*. The Addenbrooke’s Cognitive Examination Revised (ACE-R), a sensitive cognitive screening test of global cognitive functioning [35], measures 5 cognitive domains; attention/orientation, memory, verbal fluency, language and visuospatial abilities. Lower scores suggest poor cognitive performance. ACE-R is sensitive to early stages of dementia [51] and will be used as a participant screen. Adequate performance on the ACE-R is required for the participant’s data to be included in the final data sample.II.*Prospective memory* (*PM*). There will be a rigorous assessment of PM.The *Memory for Intentions Screening Test* (*MIST*) [52] is a standardised measure of PM developed for use in clinical settings. Throughout the test, participants will be required to remember and perform 4 time-based (for example; ‘in exactly 15 minutes please tell me it is time to take a break’) and 4 event-based tasks (for example: ‘when I hand you a red pen, please sign your name on the paper’). A series of word search puzzles will be provided as a distractor task to prevent overt rehearsal of the prescribed intentions. The researcher will monitor whether the participant remembers to perform the PM tasks correctly. Errors and scoring will be assessed in accordance with the MIST professional manual, which allows for an assessment of eight differing aspects of PM functioning. The MIST takes 30 minutes to administer. Total scores range from 0 to 48 with higher scores indicating better performance on the task. The MIST is sensitive to various neurological disorders, such as mild cognitive impairment [53] and has good reliability and validity [54].The brief *Virtual Week assessment*, which involves 2 ‘virtual’ days of the computerised board game, will assess event-based and time-based PM tasks. Based on our previous study with HF patients [55], the brief version of Virtual Week will take 30 to 45 minutes to complete.The *Naturalistic PM task* assesses 2 types of time-based PM tasks: 1) an appointment task at a set time of day and 2) one requiring monitoring a short interval of time. The latter is typical of many laboratory-based PM tasks. Participants will be asked to ring a prescribed number at 2 set times over 3 consecutive days. With each scheduled phone call, a recorded message will ask participants to call back after an interval of 5, 10 or 20 minutes.III.*Timed Instrumental Activities of Daily Living* (*TIADL*). Participants’ level of independence in daily activities will be assessed using a modified version of the TIADL [56]. Participants are required to complete nine activities that are relevant to tasks they would perform at home. The original five tasks are functional measures basic to independent living such as telephone communications, financial abilities, nutrition, shopping and medication use. Four additional tasks that are more relevant in the current technological communication environment and specifically related to HF self-care have been adapted for this study: 1) checking and sorting the sodium content of 3 food packages from the lowest to the highest amount of sodium; 2) extracting health information from a computer screen simulating a webpage to estimate a target heart rate for exercise; 3) extracting data from a webpage to look up a specified train timetable, and 4) finding a matching pair of black socks in a laundry basket full of mixed single socks. Participants are scored on the length of time to complete each of the nine activities, and if any, the type of error in performing the activity. Shorter completion times indicate better performance. The rapid and efficient completion of these tasks is advantageous in daily life and the time taken to complete the tasks is an objective indication of functional independence [56]. This assessment will be a key strength to the study, providing an objective and sensitive behavioural measure to evaluate the effectiveness of the cognitive training intervention on everyday functional independence.IV.*Working memory and executive functioning*. A battery of tests from the CogState program will be used (www.cogstate.com) [57,58]: i) The One Back Task assesses working memory. Participants are presented with a succession of playing cards on a screen and must decide if the card displayed is the same as the one presented immediately before; ii) The Two Back Task is presented in the same way as the One Back Task: however, participants are required to decide if the card displayed on screen is the same as a card presented two cards previously. Responses that are more accurate reflect better working memory, on both tasks; iii) The Detection Task measures psychomotor functioning and speed of processing. Participants must respond as quickly as possible to a card flipping over on screen, by pressing a button on the keyboard. Reaction time is measured and lower scores indicate better performance; iv) The Identification Task measures visual attention. Participants must decide whether a playing card presented on screen is red, by pressing the ‘Yes’ or ‘No’ button. Reaction time is measured and lower scores indicate better performance; v) The One Card Learning Task measures visual learning and memory. Participants are presented with a succession of playing card on screen, and must decide if the card currently displayed has been displayed previously. Accuracy of performance is measured, with higher scores indicating better performance. In addition to the computer battery of tests that take only 8 minutes to complete, there will be a pen and paper task, the Trail Making Test (TMT) [59], which assesses planning ability. It consists of two parts: Part A and B. In Part A, participants are required to draw lines to connect circles that are numbered consecutively; in Part B, participants connect circles that are numbered or lettered, alternating between the numeric and alphabetic sequences. This test takes approximately 5 minutes to complete, and the participant’s score is the total time taken to complete the task. Lower scores on the TMT indicate higher levels of planning ability.V.*Verbal memory*. In the Hopkins Verbal Learning Test-Revised [60,61], participants must listen to a list of 12 words read out by the experimenter, and then verbally recall as many words as possible from that list. This same procedure is repeated two more times. The participant is then asked, after a 20- to 25-minute interval, to verbally recall the same list of words. Following this final trial, the researcher reads out a list of 24 words and the participant is asked to identify the words that were presented in the original list of 12 words. This verbal memory test assesses episodic memory and the delayed recall test is particularly sensitive to ageing and abnormal ageing. The test has been successfully used in clinical and healthy populations of older adults [62].VI.*Premorbid intelligence*. The National Adult Reading Test (NART) [63] is a word-recognition test of vocabulary knowledge that requires participants to read aloud 50 English words of increasing difficulty that do not follow normal phonetic rules: for example, ‘chord’. This test takes about 5 minutes to complete and responses are audio-recorded for scoring purposes. The NART is widely used as an estimate of premorbid ability given the premise that reading ability is relatively independent of brain damage. Furthermore, NART performance appears to be impervious to the effects of many neurological and psychiatric conditions [64]. In a retrospective validity study of the NART, there was a strong correlation (*r* = 0.73; *P* < 0.001) between Intelligence Quotient (IQ) age 11 and NART performance at age 77 [64]. The NART will be used to characterise the HF sample and match the healthy non-HF controls on premorbid intelligence.

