
### Measures to be collected from healthy control group

The healthy control group will be matched to the HF patient group on age, premorbid intelligence and gender, and will undergo neuropsychological assessment as described above and highlighted with asterisks in Table 1. Psychosocial demographics, including social support and anxiety and depression, will also be collected to allow comparisons of the healthy controls and HF participants.

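### For the baseline comparison with healthy controls (aim 1), the two groups enter under different event windows and only the patients are screened for computer skills; neither the matching nor the analysis allows for this

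*Protocol article*

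**What the plan says.** The first aim in the protocol article (Study aims and objectives) is to "compare and confirm cognitive deficits, including PM deficits, of HF patients relative to healthy matched control group". The entry rules for the two groups are as follows.

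- **Events, HF patients** (Participant exclusion criteria): excluded for "a cerebrovascular accident, acute myocardial infarction or have undergone cardiac surgery in the previous 3 months". The sentence opens with a documented history of cognitive impairment or dementia and then runs on into these events.
- **Events, controls** (same section): excluded if they "have experienced a cardiac event within the past 6 months (cerebrovascular accident, acute myocardial infarction or cardiac surgery").
- **Computer use, HF patients** (same section): the rule bars those who "do not have access to a PC computer; do not have basic computer skills". Being physically unable to operate a keyboard is a further ground for exclusion.
- **Computer use, controls**: no such rule. Participant inclusion criteria says "Healthy control participants will be living independently in the community without a medical diagnosis of HF" and adds adequate performance on the ACE-R.
- **Matching**: "The healthy control group will be matched to the HF patient group on age, premorbid intelligence and gender" (Measures to be collected from healthy control group; Recruitment says the same).
- **Tests shared by both groups** (Table 1, footnote a): MoCA; MIST, brief Virtual Week and the naturalistic task; CogState, N-Back and Trail Making; NART; SF-12; HADS.
- **Analysis** (Statistical analyses): t-test and ANOVA for this comparison, with no covariate named.

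No reason is given for the different windows or for the one-sided computer rule.

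**The concern.** A non-randomised group comparison relies on entry rules, matching and adjustment to make the groups alike in everything but the factor of interest. Here the entry rules differ on two things that can move the scores.

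Stroke and cardiac events bear on cognition; the Background itself lists cerebral infarction among the routes to cognitive change in HF. If patients with an event 3 to 6 months ago are tested and controls with the same history are not, the HF deficit can be exaggerated.

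Computer familiarity works the other way. Every patient has basic computer skills, but some controls may not. Controls who struggle with the equipment lower the control mean on Virtual Week and CogState and so hide part of an HF deficit. MIST, Trail Making, MoCA and the naturalistic task are not computer tests and are not affected.

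The two effects cannot be relied on to cancel, because one acts on all tests and the other only on some. At stake is how far an aim 1 result can be read as a difference between comparable groups.

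**Working it through.** **Step 1. The two readings of the patient sentence.**

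| Event and time before entry | Patients, 3 months applies to all three events | Patients, 3 months applies to surgery only | Controls |
|---|---|---|---|
| Stroke or infarction, under 3 months | excluded | excluded | excluded |
| Stroke or infarction, 3 to 6 months | admitted | excluded | excluded |
| Stroke or infarction, over 6 months | admitted | excluded | admitted |
| Surgery, under 3 months | excluded | excluded | excluded |
| Surgery, 3 to 6 months | admitted | admitted | excluded |
| Surgery, over 6 months | admitted | admitted | admitted |

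On the first reading the groups differ only in the 3 to 6 month band, with patients the less strictly screened group. On the second, patients are the stricter group for stroke and infarction over 6 months old, so the bias from those events reverses. The groups differ on either reading.

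**Step 2. Precision of the comparison.** Sample size gives 60 HF patients for this comparison, and Study design gives 60 controls. It claims power for moderate effects but states neither a power nor a numeric effect, so there is no figure to reproduce. Assume d = 0.5 and two-sided alpha 0.05:

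- Standard error of a standardised difference = √(1/60 + 1/60) = 0.183 SD.
- Power at d = 0.5 is 77.5% (t) or 78.2% (normal). 80% power needs d = 0.516, which fits the loose wording.

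**Step 3. Possible size of each bias.** Shift in a group mean = share affected × score deficit in SD. All shares and deficits are assumptions.

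*Event window, first reading (exaggerates the deficit):*
- 5% of patients × 0.5 SD = 0.025 SD
- 10% × 1.0 SD = 0.10 SD, which is 0.10/0.5 = 20% of a moderate effect
- With no true HF effect, the rejection rate at 60 v 60 is 5.2% and 8.4% respectively, against a nominal 5%.
- Wider range, 2% × 0.3 SD to 20% × 1.0 SD: 0.006 to 0.20 SD, with rejection rate 5.0% to 19.2%.

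*Computer rule (masks the deficit, computerised tests only):*
- 10% of controls × 0.5 SD = 0.05 SD
- 20% × 0.5 SD = 0.10 SD
- Power at a true d = 0.5 falls from 77.5% to 68.6% and 58.4% respectively.
- Wider range, 5% × 0.5 SD to 30% × 1.0 SD: 0.025 to 0.30 SD, with power 73.3% to 19.2%.

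**Step 4. Against the noise.** The upper end of each moderate range, 0.10 SD, is 0.10/0.183 = 0.55 of a standard error.

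**The case against.** A stricter health rule for a healthy reference group is a common design choice, and aim 1 is worded as a comparison with such a group, not as a causal attribution to HF. Infarction and cardiac surgery can be part of the HF disease process, and the Background presents cerebral infarction as a pathway from HF to impairment. Equal windows would therefore not isolate HF. The PC rule serves home training, which controls do not do. The control sentence puts the same three events under one window, which makes a shared window for patients the more natural reading. All of this stands, and it limits the point.

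Three stronger readings are tempting but not supported:

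- A reader might infer that the HF deficit is mixed with recent stroke, infarction and surgery in general. On the natural reading, events under 3 months are excluded in both groups and those over 6 months are admitted in both.
- A reader might infer that the trial bars any patient with a past infarction. That rests on the less plausible parse; it is a reason to reword, not a finding about who was enrolled.
- A reader might infer that controls are unscreened for vision, hearing and English because only patients have that criterion. The second-interview description says "Adequate performance on the ACE-R is required" for data to enter the final sample, and controls must pass the ACE-R too. Matching also needs a NART score, obtained by reading English words aloud. Gross problems would largely be caught.

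What the objection does not answer is the unexplained 3 to 6 month difference, the ambiguous sentence, and the lack of a basic-skill check for controls who take the same computerised tests.

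**Conclusion.** The point holds as a modest, cheaply corrected weakness in aim 1. The event windows differ, the patient sentence is ambiguous, and the computer-skill rule is one-sided; the stated matching and analysis deal with none of these.

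The size cannot be computed from the documents, which give no share of patients with events in the relevant band and no share of controls lacking computer skills. The moderate assumptions give at most 0.10 SD from each source, in opposite directions, with the computer effect confined to Virtual Week and CogState. The bias is probably small, and the net direction cannot be stated.

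A reader might carry this over to the training trial. The documents do not support that: both randomised arms enter under the same patient criteria, so the randomised comparison is not biased. The ambiguous sentence does matter for describing who was eligible, but not for the fairness of the arms.

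**What to change.** 1. **Reword the patient exclusion** so that stroke, infarction and cardiac surgery each carry an explicit window. Reconcile the two groups' criteria or give the reason for the difference. Which window applies is for the investigators to state.
2. **Apply the basic computer-skill and keyboard criteria to controls.** Home PC access need not be copied, since it serves training.
3. **Record computer familiarity in all participants.** Trial status says the study is recruiting, so a new rule would leave a mixed control group. Adjust for familiarity, or run a sensitivity analysis without controls who do not meet the rule. A graded measure is better for adjustment. A yes/no item would be constant among patients and give the same group contrast as leaving those controls out.
4. **Record event dates in both groups** and repeat the aim 1 comparison in HF patients who also meet the controls' event window. If the sentence proves to mean any past stroke or infarction, restrict the controls correspondingly. Who is randomised is unchanged.

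Cost: one rewritten sentence, a few screening questions, and event dates (patients' clinical history is already collected). A few volunteer controls are turned away and a few HF patients leave one analysis. At the assumed 10%, that is 6 of 60, and the standard error moves from 0.183 to √(1/54 + 1/60) = 0.188 SD.
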